## Background

There is increasing evidence that prior pregnancies ending with delivery by in-labour caesarean (CS) are associated with both spontaneous preterm birth(sPTB), i.e. delivery < 37 weeks completed gestation, and mid-trimester loss (MTL), i.e. pregnancy loss between 14 and 24 weeks, in subsequent pregnancies. A retrospective analysis of US cohort data demonstrated that full dilatation CS (FDCS) is associated with a six-fold increased risk of sPTB compared to first stage CS [1]. Adding to this concern is the high risk of a recurrent sPTB in this group of women [2, 3]. A recent study reported that the relative risk (RR) of recurrent sPTB at < 37 weeks gestation is 2.7 for all emergency caesarean sections (EMCS) and 3.1 for a full dilatation CS (FDCS), when compared to women with a prior sPTB and without EMCS as a risk factor [2]. This risk further increases when including MTL as an outcome, with 25.4% delivering at < 24 weeks of gestation (RR 5.65) [2]. Another study demonstrated a 41% absolute risk of recurrence of sPTB at < 30 weeks of gestation [3].

The relationship between sPTB, MTL and in-labour caesarean may be related to inadvertent cervical damage at the time of CS (cervical caesarean damage, CCD). At the time of in-labour caesarean, the surgical incision itself, or surgical site extensions, may be near or within the cervical tissue. This could disrupt the integrity of cervical tissue, leading to a cervical scar defect and resulting in compromised cervical function in future pregnancies [4]. The extent of CCD may also be influenced by the suture material at the time of caesarean section, the healing process and incidence of post-operative infection.Treatment modalities to reduce sPTB are currently limited but include cervical cerclage insertion [5]. There are three options for prophylactic suture placement: low vaginal or high vaginal cervical sutures (known as transvaginal cerclages - TVCs) or transabdominal cerclage (TAC). TVCs are placed during pregnancy, while TACs, placed at the level of the internal os, require laparotomy or laparoscopy either prior to pregnancy or in pregnancy [6]. In the UK, TACs are usually reserved for women who have had a trachelectomy or a failed vaginally placed cerclage, where they are known to be highly efficacious [6].

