### Data analysis

A data analysis plan has been prepared prior to commencement of study recruitment. Maternal, pregnancy, and surgical procedure characteristics will be presented with counts and percentages for categorical variables, mean and standard deviation for continuous Gaussian distributed variables, and median and interquartile range for continuous non-Gaussian variables.

All primary and secondary outcomes, and the components of the primary outcome will be summarised by treatment arm and Group (A or B) using frequencies and percentages.

In addition, relative risk will be calculated for the treatment effect (TAC vs. TVC) with 95% confidence intervals. An interaction test will be carried out to examine whether the treatment effect is significantly different between groups A or B. Where a difference is detected, separate relative risks will be presented for both groups. Where there is a significant treatment effect, Risk differences and Number Needed to Treat (NNT) will also be presented, with confidence intervals if significant. All these analyses will be corrected for the minimisation variable and Group (A or B).

The primary analyses will be by modified intention-to-treat for the pre-conception trial arms. Women who did not conceive, suffered an early miscarriage or are lost to follow-up will be excluded. A TVC will not be inserted in a non-pregnant patient (in line with standard clinical care) and therefore these participants will be removed from the trial, at the end of the 18-month recruitment period, so that the results relate to the number of stitches actually placed.

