### Power calculation

A sample size estimation on data utilised data from a previous observational study performed by our group. This calculated that calculated that a TAC should provide a relative risk reduction of 67% for PTB < 30 weeks compared to TVC in this high-risk cohort of women (unpublished data). A total of 40 women in each intervention group (TAC/TVC) is required for 80% power, at 5% significance level, to show a significant difference between the two groups. This would equate to a total of 160 women in the study; 40 x group TVC vs. 40 x TAC in both groups: Group A (in pregnancy) and Group B (prior to pregnancy). The recruitment target accounts for a potential drop-out rate of 50% of Group B participants who may not have a subsequent pregnancy after randomisation; as informed by the MAVRIC trial [7].

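### The adjusted risk difference and NNT, with their intervals, are to be presented only after a significant result, so they are missing when the result is uncertain

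*Protocol article*

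**What the plan says.** The Data analysis section of the protocol article has three layers of reporting.

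- Descriptive, unconditional: every primary and secondary outcome, and each component of the primary outcome, is "summarised by treatment arm and Group (A or B) using frequencies and percentages".
- Relative effect, unconditional: "relative risk will be calculated for the treatment effect (TAC vs. TVC) with 95% confidence intervals". Group-specific relative risks follow only if the interaction test finds a difference between Groups A and B.
- Absolute effect, conditional: "Where there is a significant treatment effect, Risk differences and Number Needed to Treat (NNT) will also be presented, with confidence intervals if significant".

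The section then adds: "All these analyses will be corrected for the minimisation variable and Group (A or B"). So the RD that depends on significance is an adjusted one.

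The Power calculation section sets the scale. It assumes a "relative risk reduction of 67% for PTB < 30 weeks compared to TVC". On trial size it says: "A total of 40 women in each intervention group (TAC/TVC) is required"; the design has 80% power and a 5% level. That is 40 per arm within each Group, or 80 per arm with the Groups pooled.

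**The concern.** Which effect estimates appear in the report should not depend on the p-value. An RD interval is most useful after a non-significant result, because it shows how large a benefit remains compatible with the data. The rule removes it at that point. The choice between an abdominal and a vaginal procedure turns on absolute benefit against absolute harm, so the absolute scale should not be optional here.

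There are two further defects.

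- RDs shown only after significance are a selected set and on average exceed the true difference.
- The rule is not well defined. It does not say which scale or test decides significance. Its second condition, on the confidence intervals, is either redundant (significance has already been required) or allows an RD or NNT to be printed without an interval.

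This is not detail left to an analysis plan. The article states the rule, and an analysis plan that follows it inherits the problem.

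**Working it through.** **Inputs.** RR at the design effect 1 − 0.67 = 0.33; 40 per arm per Group; 5% level, taken as two-sided (sidedness is not stated); all from Power calculation. That section gives no TVC event rate, so I assume a range from the Background: 41% ("41% absolute risk of recurrence of sPTB at < 30 weeks of gestation") to 46% (the failure rate quoted for TVC after in-labour caesarean).

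**Reproducing the plan's figure.** With p1 the TVC risk, p2 = 0.33 p1 and p̄ their mean,

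n = [1.96·√(2p̄(1−p̄)) + 0.8416·√(p1(1−p1) + p2(1−p2))]² / (p1−p2)².

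For p1 = 0.41: p2 = 0.1353, p̄ = 0.27265, n = (1.2343 + 0.5042)² / 0.2747² = 3.0225 / 0.07546 = 40.05, rounded up to 41. Power at 40 per arm is 79.9%. For p1 = 0.46, n is 34, or 41 with a continuity correction. The stated 40 is reproduced, so 41–46% is a reasonable range.

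**Effect of the rule.** For each true RR, I enumerated all pairs of binomial counts exactly and applied the unadjusted pooled z-test (|z| > 1.96). Not shown = 1 − P(significant). Mean RD when shown = E[RD | significant]. Ratio = that mean divided by the true RD. RDs are in percentage points.

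| Per arm | True RR | TVC risk | True RD | Not shown | Mean RD when shown | Ratio |
|---|---|---|---|---|---|---|
| 40 | 0.33 | 41% | 27.5 | 19.1% | 30.6 | 1.12 |
| 40 | 0.33 | 46% | 30.8 | 13.3% | 33.2 | 1.08 |
| 40 | 0.5 | 41% | 20.5 | 48.9% | 28.3 | 1.38 |
| 40 | 0.5 | 46% | 23.0 | 41.6% | 29.9 | 1.30 |
| 40 | 0.6 | 41% | 16.4 | 65.9% | 27.5 | 1.67 |
| 40 | 0.6 | 46% | 18.4 | 59.8% | 28.6 | 1.55 |
| 80 | 0.33 | 41% | 27.5 | 1.8% | 27.8 | 1.01 |
| 80 | 0.33 | 46% | 30.8 | 0.7% | 31.0 | 1.00 |
| 80 | 0.5 | 41% | 20.5 | 18.5% | 22.8 | 1.11 |
| 80 | 0.5 | 46% | 23.0 | 12.5% | 24.7 | 1.07 |
| 80 | 0.6 | 41% | 16.4 | 39.2% | 21.0 | 1.28 |
| 80 | 0.6 | 46% | 18.4 | 32.2% | 22.4 | 1.21 |

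**What is lost in one trial.** Take 16/40 on TVC against 9/40 on TAC. RR = 0.225/0.40 = 0.56 (95% CI 0.28 to 1.12), z = 1.69. RD = 17.5 points, SE = √(0.4·0.6/40 + 0.225·0.775/40) = 0.1018, 95% CI −2.4 to 37.4. The plan prints the RR line and omits the RD line.

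**Ambiguous trigger.** Take 16/40 against 8/40.

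- RR = 0.50, SE(log RR) = √(1/8 − 1/40 + 1/16 − 1/40) = 0.371, 95% CI 0.24 to 1.03, which includes 1.
- RD = 20 points, SE = √(0.006 + 0.004) = 0.10, 95% CI 0.4 to 39.6 points, which excludes 0.

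Whether the RD is presented depends on a choice that the text does not make.

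**Sparse harms.** Suppose a serious complication occurs in 3/80 on one arm and 0/80 on the other. The RR is zero or undefined, with no usable standard interval. The RD is 3.75 points (Newcombe 95% CI −1.5 to 10.5). With pooled z = 1.75 and Fisher p = 0.25, it would not be presented if the rule covers harms.

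**The case against.** A reader might infer that absolute effects are hidden after a non-significant result and that absolute harms would never be reported, leaving benefit without harm. The document does not support this. Counts and percentages by arm and Group are promised for every secondary outcome with no significance condition, and the serious procedural complications, sepsis, ITU admission and maternal death are on that list. With the RR and its interval also unconditional, a crude RD and interval can be derived. What stands is narrower: the adjusted RD cannot be rebuilt from arm percentages.

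A reader might also infer that any RD the trial prints will be inflated because of this rule. That goes too far. Inflation is an average over trials selected for significance. In a single significant trial the RD is the same number with or without the rule, and the RR in that trial has passed the same filter. At the design effect the inflation is modest, and the larger ratios need a true effect well below a 67% reduction. The 40-per-arm rows are also not the default: Group-specific relative risks appear only if an interaction is found, so the 80-per-arm rows describe the main analysis. On the other side, the 67% rests on the group's own unpublished observational data, so smaller true effects are plausible.

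Two smaller points have merit. The sentence does not name its outcomes, so its application to harms is a natural reading but not certain. And the NNT interval is discontinuous when the RD interval spans zero, which may explain the second condition. That is a reason for care with the NNT, not for withholding the RD.

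**Conclusion.** The concern holds in limited form. The article fixes a significance-dependent reporting rule for the adjusted RD and NNT and their intervals. In the pooled analysis the rule would rarely bite if the design effect is true (about 1–2% of trials), but it would withhold the adjusted RD in about 13–19% of trials at RR 0.5 and 32–39% at RR 0.6. Within one Group the figures are about 13–19%, 42–49% and 60–66%. Average inflation of the RDs shown runs from about 1.01 (pooled, design effect) to about 1.7 (one Group, RR 0.6).

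These sizes assume a TVC risk of 41–46%, a two-sided test, an unadjusted analysis and, for the pooled rows, the same risks in both Groups. The case for change does not depend on the exact figures: the condition serves no purpose, and its trigger is undefined.

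**What to change.** Delete both significance conditions from the sentence. In their place:

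- **Primary outcome:** report the RD corrected for the minimisation variable and Group, with 95% CI, beside the RR whatever the p-value, overall and by Group wherever Group results are shown.
- **Serious complications:** give counts by arm and, where events are sparse, an unadjusted RD with a small-sample interval such as Newcombe's. An adjusted model may not be estimable with zero cells.
- **NNT:** give it only as a figure derived from the RD. When the RD interval includes 0, express its interval as NNT-benefit to NNT-harm, or omit the NNT.

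The cost is a rewritten sentence, a few table columns, and a named method for the adjusted RD in the analysis plan if it does not already have one. Sample size, alpha and data collection are unaffected. Always reporting removes the selection across trials; it does not change the RD printed in a trial that turns out significant.

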### Schedule of assessments

Following randomisation, the allocated procedure will be arranged. Participants in Group A will have the cerclage (TAC or TVC) inserted prior to 14 + 0 weeks’ gestation. Group B participants allocated to TAC will have the procedure placed before their next pregnancy and those allocated to TVC will have it placed during their next pregnancy before 14 + 0 weeks’ gestation. TACs are performed as an open or laparoscopic procedure under either regional or general anaesthetic, and may require an inpatient stay of up to three days. TVCs will be performed at the participant’s local maternity unit with the insertion technique and anaesthesia according to clinician’s discretion and local practices. TACs will usually remain in situ (to support any future pregnancies) while TVCs are removed at around 37 weeks’ gestation. TACs are more specialised procedures and so they may be carried out in designated specialist units, as per local practice. The timeframe between randomisation and study procedure is flexible from site to site, depending on theatre list availability, although all procedures must be carried out before the participant is 14 + 0 weeks’ pregnant.

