### Data collection

Data will be collected by attending clinician or research midwives and includes: at randomisation - participant background: demographic characteristics, risk factors, obstetric history; before pregnancy trial intervention procedure (Group B – TAC); during pregnancy - trial intervention procedures (Group A - TVC or TAC, Group B – TVC); clinical care: preterm surveillance methods and test results, e.g. infection screening, cervical length measurements, caesarean section scar characteristics, predictive biomarker tests, concomitant treatments; after pregnancy - outcomes: e.g. onset of labour, gestation at delivery, infection, admission to ITU (mother) and/or neonatal unit (baby).

Data will be stored on the ABOVE Trial Database, which is hosted within the already established PCN Database (www.medscinet.net/ukpcn). This is a secure web-based platform containing standardised clinical information regarding women at high risk of sPTB. The ABOVE database’s data monitoring facility will be used to ensure data quality [10]. This function allows efficient and remote raising and answering of queries by the central and site trial teams.

The data collected will allow us to evaluate the effectiveness of the interventions on preventing poor outcomes, whether there are differences between women from different groups (demographic characteristics and risk factors) and whether treatment effects are compounded by other variables, such as intensity of preterm surveillance and concomitant treatments.

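### In Group B the conception-based exclusion removes TAC women after their surgery; if it also governs the maternal harm outcomes, a hysterectomy or death at pre-conception TAC cannot be counted

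*Protocol article*

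**What the plan says.** All references are to the protocol article.

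- **Schedule of assessments** fixes the timing: "Group B participants allocated to TAC will have the procedure placed before their next pregnancy". Group B women allocated to TVC have it placed during the next pregnancy.
- **Data analysis** sets the population: "The primary analyses will be by modified intention-to-treat for the pre-conception trial arms". It continues: "Women who did not conceive, suffered an early miscarriage or are lost to follow-up will be excluded". After noting that a TVC is not placed in a non-pregnant woman, it says that "these participants will be removed from the trial, at the end of the 18-month recruitment period", and gives the reason: "so that the results relate to the number of stitches actually placed".
- **Secondary outcomes** (maternal) include serious complications of the trial intervention (bladder injury, bowel injury, intraoperative membrane rupture, cervical tear, hysterectomy), and also maternal sepsis, ITU admission and maternal death. Data analysis says that all secondary outcomes are summarised by arm and Group. It names no separate set for them.
- **Power calculation** allows for "a potential drop-out rate of 50% of Group B participants who may not have a subsequent pregnancy after randomisation".
- **Data collection** lists procedure data before pregnancy for Group B TAC. Infection and ITU admission appear among its examples of outcomes collected after pregnancy.

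**The concern.** Two things go wrong when these sections are read together.

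First, the rule does not do what its reason says. A Group B woman allocated to TAC who never conceives already has her stitch. Removing her makes the results depart from the number of stitches placed. The reason fits TVC only.

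Second, the exclusion depends on something that happens after surgery in one arm, and in some cases the surgery itself would cause it. A woman who has a hysterectomy at pre-conception TAC, or dies from it, cannot conceive, and so cannot enter a set restricted to women who conceived. If that set is used for the maternal harm outcomes, the Group B TAC count of these events from that procedure is zero whatever the true rate. Complications that do not affect fertility are not pushed in one direction, but they are counted in fewer women.

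The trial is meant to inform practice guidelines, and pre-conception TAC is the arm in which a woman accepts abdominal surgery without knowing whether a pregnancy will follow. Harm in operated women who do not conceive is part of that decision.

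**Working it through.** **1. The plan's own figure.** Power calculation gives 40 per arm in each Group, 80% power, 5% significance and a 67% relative risk reduction (RR 0.33). It names no control rate. One figure in the Background, a 41% recurrence risk before 30 weeks, is used here as an assumption, with a two-sided test. Then p1 = 0.41 and p2 = 0.33 × 0.41 = 0.135, and

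n = [1.96·√(2p̄(1−p̄)) + 0.84·√(p1(1−p1) + p2(1−p2))]² / (p1 − p2)²

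This gives 41 per arm, and 79.9% power at n = 40. With the Background's 46% TVC failure rate the result is 34, or 41 with continuity correction. The 40 per arm is therefore reproduced closely enough to use as the evaluable number.

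**2. Women randomised in Group B.** With non-conception d, 40 evaluable per arm needs 40/(1 − d). At the plan's d = 0.5 this is 40/0.5 = 80 per arm. The text does not state the inflated total, and the flowchart is not shown, so 80 is derived.

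**3. Operated women dropped.** Assume that all 80 Group B TAC women are operated on and that d is the same in both arms. Then 80 − 40 = 40 operated women leave the analysed set. That is half of the pre-conception TACs, and 40/(80 + 40) = one third of all TACs once the 40 in Group A are added. In Group B TVC, no woman leaves after a stitch because of non-conception, since TVC is placed only in pregnancy.

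**4. What zero events would show.** The exact two-sided 95% upper limit with no events is 1 − 0.025^(1/n):

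- n = 40: 1 − 0.025^(1/40) = 8.8%
- n = 80: 1 − 0.025^(1/80) = 4.5%

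**5. Sensitivity to the non-conception rate** (40 retained throughout, so the limit under the exclusion stays at 8.8%; numbers rounded up):

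| Non-conception | Operated, 40/(1 − d) | Dropped | Zero-event upper limit, all operated |
|---|---|---|---|
| 20% | 50 | 10 | 7.1% |
| 30% | 58 | 18 | 6.2% |
| 40% | 67 | 27 | 5.4% |
| 50% | 80 | 40 | 4.5% |
| 60% | 100 | 60 | 3.6% |

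**6. Complications unrelated to conception.** The article gives no complication rate. At assumed rates of 1%, 2% and 5%, the expected Group B TAC events are 0.8, 1.6 and 4.0 in 80 women, against 0.4, 0.8 and 2.0 in 40. The expected proportion is the same, so the loss is one of precision.

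**7. Events that prevent conception.** No rate is needed. Every hysterectomy or death at pre-conception TAC falls in the excluded group, so the analysed count from that procedure is zero at any true rate.

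**The case against.** The strongest reply concerns scope. The exclusion follows a sentence about the primary analyses, and the primary outcome cannot be observed without a pregnancy, so restricting it to women who conceive is understandable there. The sentence on summarising secondary outcomes comes earlier and carries no such restriction. The article mentions a separate analysis plan, not shown here, which may define a safety population. The participants to be removed from the trial may also be only the TVC-allocated women who never received a stitch, since the sentence begins with TVC. This lowers the certainty: use of the set for harm outcomes is an inference from the article's wording, and the point is conditional on it. It does not remove the problem. The exclusion sentence covers both pre-conception arms, removal from the trial is wider than removal from one analysis, no exception is made for complications, and the stated reason is contradicted for TAC on any reading that includes TAC women.

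A second reply is that nothing is hidden: pre-conception procedure data are collected, the DMC reviews serious adverse events, and adverse events are reported under regulations. That stands as oversight, but it does not place the events in the reported comparison between arms.

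A reader might go further and infer that the whole complication list is lost from the TAC arm. The document does not support that. The exclusion concerns the pre-conception arms, so Group A TAC is untouched. Group B TAC women who stay in the analysed set still contribute. Intraoperative membrane rupture cannot occur at a procedure done before conception.

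**Conclusion.** The point holds in a limited and conditional form. As written, the Group B rule drops TAC women after surgery and so contradicts its own stated reason. If the same set is used for the maternal secondary outcomes, which the article does not rule out, hysterectomy and death at pre-conception TAC are excluded by construction, and other surgical complications are counted in fewer women without a built-in direction of bias.

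The size is about 40 of 80 operated Group B women, with a zero-event upper limit of 8.8% instead of 4.5%. This rests on 50% non-conception in each arm and on every allocated TAC woman being operated on. The plan calls the 50% only a potential rate; at 30% the loss would be about 18 of 58.

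It would be too strong to conclude that the trial's risk-benefit assessment of pre-conception TAC will be unsound. The documents give no complication rate, the unseen analysis plan may already keep these women in a safety set, and the underlying procedure data exist.

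**What to change.** In Data analysis:

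1. Limit the exclusion for non-conception and early miscarriage to pregnancy and neonatal outcomes.
2. State that procedure complications, maternal sepsis, ITU admission and maternal death are reported for all women who had a trial procedure, and also by randomised arm, in both Groups, whether or not they conceived.
3. Reword the removal sentence so that it says which participants it covers and agrees with the reason given for it.
4. Show non-conception and early miscarriage by arm beside the safety results.

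The cost is small: a few sentences and one added safety table, with no change to sample size or to the primary analysis. One check is needed. Procedure data for Group B TAC are already collected before pregnancy, but infection and ITU admission are listed only among the after-pregnancy outcomes. The sponsor should confirm that sepsis, ITU admission and death are captured for operated women who never conceive, and add those items to the pre-pregnancy data collection if they are not.

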Treatment modalities to reduce sPTB are currently limited but include cervical cerclage insertion [5]. There are three options for prophylactic suture placement: low vaginal or high vaginal cervical sutures (known as transvaginal cerclages - TVCs) or transabdominal cerclage (TAC). TVCs are placed during pregnancy, while TACs, placed at the level of the internal os, require laparotomy or laparoscopy either prior to pregnancy or in pregnancy [6]. In the UK, TACs are usually reserved for women who have had a trachelectomy or a failed vaginally placed cerclage, where they are known to be highly efficacious [6].

TVCs are widely used to prevent sPTB in high-risk women [6]. However, retrospective studies show that they are ten-fold less effective in women who have had a sPTB following an in-labour CS, compared to other high-risk groups, with failure rates of 46% [4]. Conversely, TAC has a success rate of > 90% in high-risk women [7]. Another retrospective cohort study demonstrated that TAC was associated with less sPTB at < 30 weeks compared to TVC [8]. Moreover, women with a history of preterm birth and mid-trimester pregnancy loss report having a TAC in place reassuring [9].

Efficacy of TAC is thought to be related to the position of the suture above the scar. In pregnancy this may not be possible due to the implantation site and the inherent dangers of inserting a suture near the embryonic sac. Furthermore, increased vascularity in the pregnant cervix and an enlarged gravid uterus can make suture placement difficult. To date, there has been no comparison of outcomes from preconception and in-pregnancy TAC procedures.

In response to the accumulating, but often retrospective, evidence associating in-labour CS with MTL and sPTB, we have designed the ABOVE randomised control trial (RCT) to address this by comparing the effectiveness of TAC versus TVC in women who have had a previous sPTB or MTL following in-labour caesarean, both before and during pregnancy.

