### End of study definition

To allow time for collection of outcome data and analysis, end of study is defined as is defined as six months after the expected date of delivery of the last participant recruited.

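### Group B women who are not pregnant are removed on one calendar date, the close of recruitment; the 50% allowance is not tied to that date, so the separate 80% power claimed for Group B is unsupported, and the rule's scope by arm is unclear

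*Protocol article*

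**What the plan says.** All references are to the Protocol article.

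- **Participant recruitment** sets an 18-month recruitment period.
- **Data analysis** describes a modified intention-to-treat analysis for the pre-conception arms. It excludes women who do not conceive, miscarry early or are lost to follow-up. It then notes that a TVC is not placed in a non-pregnant woman, and that "these participants will be removed from the trial, at the end of the 18-month recruitment period". The purpose given for this removal is "so that the results relate to the number of stitches actually placed".
- **Design** says Groups A and B are separately powered, with complete data needed from 80 women in each.
- **Power calculation** asks for 40 women per arm in each Group, which "is required for 80% power, at 5% significance level", on the basis that "a TAC should provide a relative risk reduction of 67% for PTB < 30 weeks compared to TVC". It adds: "The recruitment target accounts for a potential drop-out rate of 50% of Group B participants who may not have a subsequent pregnancy after randomisation". The allowance is said to be informed by an earlier trial. No time window is given for it.
- **Schedule of assessments** places the Group B TAC before the next pregnancy and the Group B TVC during it. The wait for the procedure varies with theatre availability and no length is given.
- **End of study definition** sets the end at "six months after the expected date of delivery of the last participant recruited".

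**The concern.** The removal date is a single calendar date that coincides with the close of recruitment. The first Group B recruit has 18 months to conceive and the last has almost none. No section gives a conception window after recruitment closes. Three things follow.

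1. **Numbers.** The 50% allowance is what turns the randomised number into 80 evaluable Group B women. If it reflects conception over a fixed follow-up of a year or more, it would not carry over to a window that shrinks to zero. It also leaves out two of the three stated exclusions.
2. **Comparability of arms.** It is unclear whether the removal applies to every non-pregnant Group B woman or only to TVC women without a stitch. The two readings give different follow-up by arm.
3. **Who is analysed.** Tying results to stitches placed sits badly with an intention-to-treat label, because in Group B a TAC stitch precedes pregnancy and a TVC stitch follows it.

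The rule decides who enters the Group B primary analysis, and it is hard to repair once data exist.

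**Working it through.** **Inputs from the article.** Two-sided 5% level (sidedness assumed), 80% power, relative risk 1 − 0.67 = 0.33, 40 evaluable per arm per Group, 50% Group B allowance, 18-month recruitment.

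**Assumptions.**
- The Power calculation states no control event rate. The Background offers two candidates: "Another study demonstrated a 41% absolute risk of recurrence of sPTB at < 30 weeks of gestation", and a TVC failure rate of 46% in this population. I use 41% and give 46% as a check.
- Accrual is even and the monthly conception hazard h is constant.
- The number randomised is derived: 80/(1 − 0.50) = 160 in Group B, or 80 per arm. The flowchart with anticipated numbers is not shown.

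**The plan's own figure.** With p1 = 0.41 and p2 = 0.33 × 0.41 = 0.1353, the mean is p̄ = 0.27265.

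n = [1.96 √(2p̄(1 − p̄)) + 0.842 √(p1(1 − p1) + p2(1 − p2))]² / (p1 − p2)² = 40.05, i.e. 41 rounded up.

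Power at 40 per arm is 0.799, so the stated 40 reproduces. At p1 = 0.46 the formula gives 34, and power at 40 per arm is 0.863.

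**Yield at the month-18 cut-off.** Under even accrual the available time is uniform on 0 to 18 months, with mean 9. The share who conceive by the cut-off is

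yield = 1 − (1 − e^(−18h)) / (18h).

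If 50% conceive within W months of randomisation, h = ln 2 / W. For W = 18, 18h = 0.693 and yield = 1 − 0.5/0.693 = 0.279.

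| 50% conceive within | Yield at cut-off | Evaluable per arm (of 80) | Power, 41% vs 13.5% | Power, control rate 46% | Needed per arm for 40 evaluable |
|---|---|---|---|---|---|
| 12 months | 38% | 30 | 0.67 | 0.75 | 106 |
| 18 months | 28% | 22 | 0.54 | 0.61 | 144 |
| 24 months | 22% | 18 | 0.45 | 0.52 | 182 |

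**When is 50% met?** Setting yield = 0.50 gives h = 0.0885 per month, which means 1 − e^(−12h) = 65% conceiving within 12 months and 80% within 18. At 70%, 80% or 85% within 12 months, the yield is 54%, 62% or 67%.

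**Exclusions outside the allowance.** Suppose the 50% is met exactly. A further 10% or 20% lost to early miscarriage or follow-up (assumed) leaves 36 or 32 per arm, with power 0.76 or 0.70.

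**Scope of the removal.**
- *Both arms:* TAC women must wait for surgery before trying to conceive. With a delay of d months, yield = ((18 − d)/18) × [1 − (1 − e^(−h(18 − d)))/(h(18 − d))]. The article gives no delay. An assumed 3 months lowers the TAC yields in the table to 28%, 20% and 16%.
- *Only TVC women without a stitch:* TAC women then have no stated cut-off, and the imbalance can run the other way.

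**Pooled comparison.** Adding Group A's 40 per arm to 22 per arm gives 62 per arm and power of about 0.94.

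**End of study.** A last recruit in Group B who is not pregnant has no expected delivery date, so the definition cannot be applied to her.

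**The case against.** Several stronger readings are tempting, and the article does not support them.

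- **That the 50% cannot be reached.** This is not shown. The article gives neither a conception rate nor the window behind the 50%, and its source is not at hand. If about 65% conceive within 12 months with no delay, 50% is met; at higher rates it is exceeded. What remains is that the figure is unjustified under this cut-off and would probably be missed if it comes from follow-up of a year or more.
- **That the TAC arm is the one disadvantaged.** This holds only if the removal covers both arms, and the delay is not quantified. Only possible inequality is supported.
- **That the analysis is as-treated.** The listed exclusions are non-conception, early miscarriage and loss to follow-up. The remark about stitches gives the reason for removing non-pregnant women, and no sentence excludes a TVC woman who conceives but gets no stitch. The wording could still be read that way.
- **That the Group B comparison is biased.** Restricting to pregnancies is natural for an outcome that exists only in pregnancy, and randomisation should balance entry dates. A cut-off applied equally mainly costs numbers. Bias needs an arm-dependent delay and a link between speed of conception and outcome, and no such link is shown.
- **That the whole trial is underpowered.** The relative risk is pooled over Groups, with separate estimates only if an interaction is detected. The pooled comparison keeps good power. The shortfall bears on the claim of separate powering for Group B.

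**Conclusion.** The concern holds in limited form, with moderate confidence. The single calendar cut-off, the missing time window for the 50%, and the two exclusions left out of the allowance are all visible in the text. Together they leave the separate 80% power for Group B unsupported. The size is conditional: Group B power of about 0.67, 0.54 or 0.45 if 50% conceive within 12, 18 or 24 months, and about 0.76 to 0.70 even if the 50% is met but 10% to 20% are then lost. These figures rest on even accrual, constant hazard, 80 randomised per arm, and a 41% control rate that the Power calculation does not name. At 46% the first three become 0.75, 0.61 and 0.52. Separately, the scope of the removal by arm is ambiguous, the stitches wording conflicts with the analysis label, and the end-of-study date is undefined for a non-pregnant last recruit.

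**What to change.** 1. State one conception cut-off rule that applies identically to both Group B arms. A fixed window per woman, counted from randomisation, is preferable, with its length limited by the follow-up the sponsor can support.
2. Analyse as randomised every Group B woman whose pregnancy reaches 14+0 weeks within that rule, whether or not a stitch was placed. Delete the wording about stitches placed.
3. Tabulate conception and early miscarriage by arm for all randomised women.
4. Restate the expected Group B yield and power under the chosen rule, net of early miscarriage and loss to follow-up.
5. Define end of study by the last included pregnancy, so that the Data analysis, Power calculation and End of study sections agree.

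**Cost.** Items 2 to 5 are mainly wording and reporting, and item 4 may mean stating a lower power. Item 1 costs time if the window is long: a 12-month window plus about 9 months of pregnancy runs to roughly 21 months after the last Group B recruit, before close-out. That means longer follow-up of late recruits through routine records. If the sponsor cannot support it, a shorter window or a common calendar date is still workable, provided it is the same in both arms and the yield and power are restated to match.
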